### **6.2 ASSESSMENTS AT FOLLOW-UP**

After completion of treatment, patients should be reviewed weekly until acute side effects have resolved then 3 monthly until 1 year, 6 monthly thereafter.

Follow up visits at more frequent intervals should be undertaken at the discretion of the participating clinician.

Assessments to include:

- Clinical examination, performance status (see appendix 1), dyspnoea score (see appendix 3) and weight
- Assessment of any continuing or new toxicity (see appendix 2)
- Assessment of disease status
- Assessment of response by a contrasted CT scan thorax and abdomen within 4 weeks of cycle 4 (even if 6 cycles are given), 6 months after randomisation and 12 months after randomisation.
- Details of any additional cancer treatment received
- Late toxicity (CTCAE v3.0)

Participating sites should make all necessary efforts to ensure that follow-up information is obtained for all participants e.g. this may include methods such as tracking the patient through a national cancer registry, GP records network etc if contact is lost.

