#### Secondary end points

- Local progression-free survival
- Metastasis-free survival
- CTCAE v3.0 toxicity
- Chemotherapy dose intensity
- Radiotherapy dose intensity

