***Overall survival and local progression-free survival.***

Overall Survival is the time between date of randomisation and date of death of any cause. Survivors will be censored on the last date known to be alive. **Local progression-free survival (local control)** will be calculated from the date of randomisation to the date of first clinical evidence of progressive disease at the primary site, or death.

Kaplan-Meier curves (Kaplan and Meier 1958) will be drawn for each treatment group. Overall survival and local progression-free survival will be compared using the Mantel-Cox version of the log rank test.

- All randomized patients treated with at least one study dose of cisplatin and etoposide will be included in the comparison of proportions of grade 3 and 4 toxicities.

**Toxicity** will be assessed according to NCI Common Terminology Criteria for Adverse Events v 3.0 (see appendix 2). The proportions of patients experiencing a grade of 3 or above acute toxicity, including acute radiation morbidity, or late radiation morbidity will be compared between the treatment groups using Chi-squared and Fisher Exact tests. Acute toxicity will be defined as toxicities occurring from commencement of treatment to 3 months after completion, late toxicity will be defined as toxicities occurring between 3 months and 2 years after completion of treatment.

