Toxicity will be assessed according to NCI Common Terminology Criteria for Adverse Events V.3.0. The proportion of patients experiencing a grade of 3 or above acute toxicity, including acute and/or late radiation morbidity, will be compared between the treatment groups using  $\chi^2$  and Fisher Exact tests. Acute toxicity will be defined as toxicities occurring from commencement to 3 months after completion of treatment; late toxicity will be defined as toxicities occurring between 3 months and 2 years after completion of treatment. All patients treated with at least one dose of cisplatin and etoposide will be evaluated for tumour response and included in the analysis of tumour response rates.

Response will be assessed according to Response Evaluation Criteria In Solid Tumours (RECIST) criteria. The proportion of patients in each treatment group whose best response (up to approximately 28 days post cycle 4 or, if stopped prior to cycle 4, approximately 28 days after last chemotherapy cycle given) from randomisation is complete or partial will be compared using  $\chi^2$  and Fisher Exact tests.

Safety analyses will be performed for all randomised patients treated with at least one dose of chemotherapy. Adverse effects will be summarised and compared between the two arms. The relative chemotherapy and RT dose intensity (RDI) will be summarised by calculating the median, SD, IQR and range for patients in each randomised treatment group. The RDI will be compared between the treatment groups by using the Wilcoxon Rank Sum test.

A detailed description of patient disposition will include a summary of the following:

- ▶ All patients entered and enrolled: overall, by treatment arm and by country
- ▶ Reasons for patients entered but not enrolled
- ▶ All enrolled patients treated with study drug, by treatment arm
- ▶ Reasons patients enrolled but not treated with study drug
- ▶ Reasons patients discontinued study drug treatment
- ▶ All important protocol violations.

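### The SAP's toxicity sentence places late radiation morbidity inside "acute toxicity", against its own time windows, and no separate late comparison is clearly specified

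*Supplement*

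**What the plan says.** The SAP, which appears twice in the supplement in the same wording, specifies one grade 3+ comparison for toxicity: "The proportion of patients experiencing a grade of 3 or above acute toxicity, including acute and/or late radiation morbidity, will be compared". The tests named for it are chi-squared and Fisher exact. The two periods are then defined. The acute one starts with treatment and closes 3 months after treatment ends. For the other period the SAP states: "late toxicity will be defined as toxicities occurring between 3 months and 2 years after completion of treatment".

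The latest protocol, section 7.3.1, puts it differently: "The proportions of patients experiencing a grade of 3 or above acute toxicity, including acute radiation morbidity, or late radiation morbidity will be compared". The noun is plural, and late radiation morbidity follows an "or" after the acute item.

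The SAP also makes a general statement for the safety population: "Adverse effects will be summarised and compared between the two arms". It gives no test, grade or time window for that comparison. The protocol lists "CTCAE v3.0 toxicity" as a secondary endpoint, and section 6.2 lists late toxicity as its own item at follow-up visits.

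**The concern.** By the SAP's own definitions the acute and late windows do not overlap, so an acute proportion that includes late morbidity contradicts the sentence that follows it. An analyst must set aside either the windows or the wording of the comparison, and the choice could be made after the data are seen.

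Two hypothetical patients show what the literal rule does. The first has grade 3 pulmonary fibrosis 8 months after treatment and no earlier grade 3+ event. That event is late by definition but is counted in the acute proportion. The second has a grade 3+ event during treatment and the same fibrosis later. If one event of any kind is enough to be counted, the fibrosis adds nothing.

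Late damage is a real safety question here. The arms differ in total dose, fraction size and duration (66 Gy in 33 daily fractions v 45 Gy in 30 twice-daily fractions), and the protocol introduces its normal-tissue constraints in 4.3.2 and 4.4.2 as a means of reducing late damage.

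**Working it through.** **No figure of the plan to reproduce.** The documents state no power or sample size for toxicity. They give no late toxicity rates and no overall acute grade 3+ rate. Rates below are therefore assumptions unless a source is named.

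**Inputs from the documents**
- Patients per arm: 532 / 2 = 266 (protocol 7.1; 1:1 allocation in 3.4). This is an upper limit, since only treated patients are analysed.
- Assumed 2-year survival: 44% and 56%, mean 50% (protocol 7.1).
- Grade 3 oesophagitis in the earlier 45 Gy trial: 27% twice daily, 11% once daily (protocol, Background).

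**Assumptions**
- Late grade 3+ rates L of 5% v 12%.
- Acute grade 3+ rate A, the same in both arms, of 20%, 50% or 80%.
- Acute and late events independent; one patient-level composite.
- Two-sided 5% test.

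**Formulas**
- Pooled rate = A + (1 − A) × L. The difference between arms shrinks to (1 − A) × (L2 − L1).
- Power = Φ[(d − 1.96 × SE0) / SE1], where d is the difference, SE0 the standard error under a common rate, and SE1 the standard error under the two separate rates.

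**Separate late test, 5% v 12%**
- 266 per arm: d = 0.070, SE0 = 0.0242, SE1 = 0.0240. Power = Φ(0.94) = 0.827. With 260 per arm it is 0.818.
- Half evaluable, 266 × 0.50 = 133 per arm: SE0 = 0.0342, SE1 = 0.0339. Power = Φ(0.09) = 0.535.

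**Pooled proportion, same late rates, 266 per arm, all evaluable**

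| Acute rate A | Pooled rates | Difference | Power |
|---|---|---|---|
| 20% | 0.240 v 0.296 | 0.80 × 0.07 = 0.056 | 0.31 |
| 50% | 0.525 v 0.560 | 0.50 × 0.07 = 0.035 | 0.12 |
| 80% | 0.810 v 0.824 | 0.20 × 0.07 = 0.014 | 0.06 |

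**Larger late differences.** For 5% v 15%, power is 0.97 alone and 0.54, 0.21 and 0.09 pooled at the same three acute rates. For 10% v 20% it is 0.90 alone and 0.51, 0.21 and 0.09 pooled.

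**Effects in opposite directions.** Take the quoted oesophagitis rates as the acute rates, and assume late rates of 5% twice daily and 15% once daily.
- Twice daily: 0.27 + 0.73 × 0.05 = 0.307.
- Once daily: 0.11 + 0.89 × 0.15 = 0.244.

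The once-daily arm has three times the late rate, yet the lower pooled rate.

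**The case against.** The strongest reply is that this is careless drafting and not a new endpoint. The SAP bullet just before the toxicity paragraph speaks in the plural of proportions of grade 3 and 4 toxicities. That leaves room for comparisons toxicity by toxicity, in which neutropenia would not hide fibrosis. The SAP keeps a late definition, which has little purpose if everything is pooled. It plans a general comparison of adverse effects, and it does not withdraw the protocol's comparison. The protocol's own "or" is loose and could itself be read as a composite.

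Most of this stands, and it limits the point. A reader might infer that late toxicity will never be tested alone, or that a late difference is bound to be swamped. The documents support neither. The general comparison could include a late analysis. Swamping needs both a composite of any grade 3+ event, which the SAP does not spell out, and a high acute rate, which the documents do not give.

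The power figures also need care. Crediting a separate late test with 82-83% treats every patient as at risk throughout the late window, although the protocol assumes only 44-56% alive at 2 years. Equal acute rates in the two arms sit uneasily with the protocol's own worry about oesophagitis on twice-daily treatment.

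The reply does not remove the contradiction between two adjacent SAP sentences or the difference from protocol 7.3.1. The general statement cannot fill the gap, since it names no test, grade or window.

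**Conclusion.** The point holds as a fault in a stated rule. The only grade 3+ toxicity comparison for which the SAP names a test conflicts with the SAP's own windows and with protocol 7.3.1. Followed literally, it labels late events as acute, and no separate late test is clearly specified.

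The direction of the effect is firm if the proportion is pooled with similar acute rates in the arms. Its size is not. At 5% v 12%, even an acute rate of 20% cuts power from about 83% to 31% with all patients evaluable. The advantage of a separate test is smaller once deaths are allowed for. Its power would lie between about 53.5% and 83% as the evaluable share goes from half to all. The pooled figures also assume that everyone is evaluable. All of these figures rest on illustrative rates and on independence of acute and late events.

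Toxicity is a secondary endpoint, so the overall survival analysis is untouched.

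**What to change.** Replace the SAP sentence with two comparisons, in line with protocol 7.3.1:

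1. The proportion with grade 3+ toxicity in the acute window (start of treatment to 3 months after completion), including acute radiation morbidity. Remove the words that bring late morbidity into this proportion.
2. Separately, the proportion with grade 3+ late radiation morbidity in the late window (3 months to 2 years after completion).

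State the denominator for the second, for example treated patients alive and followed beyond 3 months after completion. That set depends on survival after randomisation, so the number in each arm should be reported with it. State also whether each proportion counts any grade 3+ event or is taken toxicity by toxicity.

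The cost is a short edit and one more unadjusted secondary safety p-value. The protocol already plans to collect late toxicity at follow-up.

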### 7.1 Sample size calculation

It is considered that a survival benefit of 12% at 2 years (in favour of once-daily radiotherapy) would be clinically significant. Using Freedman's sample size calculation based on a 2-arm trial, with a 5% significance level, 2-sided test, 80% power, and hazard ratio of 0.70, a 12% overall survival benefit at 2 years from 44% with the control arm to 56% in the experimental arm, requires a total of 506 patients. The number of deaths required is 247. An additional 5% will be added to allow for ineligible patients giving a total of 532 patients required.

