## CONVERT Statistical Analysis Plan

The analysis will be based on intention-to-treat principles (ITT). Patient data will be grouped by treatment arm according to the treatment assignments made via the MAHSC-CTU randomisation line. The primary data analysis is planned for January 2015.

The stratification factors include centre, PS (0–1 vs 2) and biochemical factors (eg, LDH, sodium, alkaline phosphatase). Comparison of data by centre will be scrutinised to identify any data inconsistencies, it will also be used to identify those centres planning to give either four or six cycles of chemotherapy. Analysis will be carried out to identify any differences between the two schedules. Other factors have been identified in previous studies to be prognostic factors and will be used to calculate the Manchester score, which gives three groupings of good, intermediate and poor prognosis; these scores will be used to compare OS and response rate.

The only planned interim analyses have been performed for the Independent Data Monitoring Committee (IDMC). Reports have been submitted to the IDMC on an annual basis starting 12 months after the first patient was randomised.

The following are the qualifications for analysis of time-to-event efficacy parameters:

- All randomised patients will be included in the analysis of overall survival (OS) and local progression free survival (ITT).

OS is the time between date of randomisation and date of death of any cause. Survivors will be censored on the last date known to be alive. Local progression-free survival (local control) will be calculated from the date of randomisation to the date of first clinical evidence of progressive disease at the primary site, or death. Kaplan-Meier curves will be drawn for each treatment group. Overall survival and local progression-free survival will be compared using the Mantel-Cox version of the log rank test.

- All randomised patients treated with at least one study dose of cisplatin and etoposide will be included in the comparison of proportions of grade 3 and 4 toxicities.

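### Late grade 3+ toxicity is compared between arms only as a crude proportion of everyone given chemotherapy, with no comparison that allows for death and unequal time at risk

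*Supplement*

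**What the plan says.** In the SAP, late toxicity covers a window of 21 months: "late toxicity will be defined as toxicities occurring between 3 months and 2 years after completion of treatment". The analysis set for grade 3 and 4 toxicity is all randomised patients "treated with at least one study dose of cisplatin and etoposide will be included in the comparison of proportions". Proportions with grade 3 or above "will be compared between the treatment groups using" chi-squared and Fisher exact tests. The latest protocol (version 3, section 7.3.1) has the same window and analysis set, and says that acute toxicity "or late radiation morbidity will be compared between the treatment groups using Chi-squared and Fisher Exact tests".

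Neither document requires a patient to be alive when the late window opens. Neither gives a rule for patients who die or are lost before it closes, and neither plans a time-to-event or competing-risks analysis of late toxicity. Kaplan-Meier curves and the log-rank test are planned only for overall survival and local progression-free survival.

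**The concern.** A proportion taken over all treated patients scores a patient who dies before having a late event as having had none. The documents do not spell this out, but it follows from the denominator. The chance of being recorded with late toxicity therefore depends on two things: how fast toxicity occurs among patients at risk, and how long patients live to be at risk.

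The trial is powered for survival to differ over nearly the same period, "from 44% with the control arm to 56% in the experimental arm" at 2 years. If that effect is real, the once-daily arm can show more late toxicity than the twice-daily arm even when the hazard among survivors is identical. If once-daily treatment shortened survival, a higher late hazard could be partly masked. A reader given one p-value cannot separate the two. This matters because late toxicity is part of a secondary endpoint in a comparison of 66 Gy with 45 Gy, and the protocol gives reduction of late normal-tissue damage as the reason for its dose constraints (sections 4.3.2 and 4.4.2).

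**Working it through.** **Check on the survival inputs.** The documents give no figure for late toxicity, so the figure to reproduce is the sample size in protocol section 7.1, calculated "with a 5% significance level, 2-sided test, 80% power, and hazard ratio of 0.70". Freedman's formula gives deaths = (1.960 + 0.842)² × (1.70/0.30)² = 7.849 × 32.11 = 252.04, rounded up to 253. With a mean 2-year death probability of (0.56 + 0.44)/2 = 0.50, N = 253/0.50 = 506, as stated. The 2-year survival figures are therefore the ones the design rests on.

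**Inputs from the documents.** 2-year survival of 44% (BD) and 56% (OD); late window from 3 to 24 months after completion of treatment, so L = 21 months; 532 patients allocated 1:1, so 266 per arm; four or six cycles at 3-week intervals.

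**Assumptions.** Exponential survival. A constant late-toxicity hazard g, equal in the two arms and set so that the 21-month risk without death would be 5%, 10%, 20% or 30%. Completion of treatment 3 or 4.5 months after randomisation.

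**Death hazards per month.** BD: −ln(0.44)/24 = 0.03421. OD: −ln(0.56)/24 = 0.02416.

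**Time at risk, completion at 3 months (window from month 6 to month 27).**
- Alive at month 6: 81.4% BD, 86.5% OD.
- Alive at month 27: 39.7% BD, 52.1% OD.
- Mean months alive in the window per patient treated, (S(6) − S(27))/hazard: BD (0.8144 − 0.3971)/0.03421 = 12.2; OD (0.8651 − 0.5208)/0.02416 = 14.2. The ratio is 1.17.

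**Crude proportion.** p = S(a) × g/(g + λ) × (1 − exp(−(g + λ)L)), where a is the start of the window and λ the death hazard. For a 20% risk, g = −ln(0.80)/21 = 0.01063:
- BD: 0.8144 × 0.2370 × 0.6100 = 11.8%
- OD: 0.8651 × 0.3055 × 0.5183 = 13.7%
- Ratio 1.16, difference 1.9 points, with no difference in hazard.

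| Late risk without death (assumed) | BD | OD | Ratio | Difference (points) | Nominal 5% test rejects |
|---|---|---|---|---|---|
| 5% | 2.9% | 3.4% | 1.17 | 0.5 | 6% |
| 10% | 5.8% | 6.8% | 1.17 | 1.0 | 7% |
| 20% | 11.8% | 13.7% | 1.16 | 1.9 | 10% |
| 30% | 17.8% | 20.7% | 1.16 | 2.9 | 13% |

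The rejection rates are normal approximations with 266 per arm. Simulating 20,000 trials gave 7.3% at 10% risk and 10.3% at 20% risk. Most rejections go against OD (for example 9.8 of the 10.2 percentage points at 20% risk).

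**Sensitivity to completion time.** Completion at 4.5 months gives ratios of 1.18, a largest difference of 3.0 points and rejection in up to 15% of trials. Completion at day 66 gives 1.15 to 1.16.

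**Sensitivity to the survival gap (20% risk, completion at 3 months).** For OD 2-year survival of 44%, 47%, 50%, 53% and 56%, the ratio is 1.00, 1.04, 1.08, 1.12 and 1.16.

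**Partial remedy.** Using as denominator only patients alive at the start of the window lowers the ratio to 1.09-1.10. It does not remove the effect, because deaths during the window still differ.

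**The case against.** The strongest reply is that nothing here is biased. A patient who dies first did not have late toxicity. With complete follow-up, the crude proportion equals the cumulative incidence with death as a competing event, which is a legitimate measure of absolute burden. That stands. The rejection rates above are false positives only for the question whether the late hazard differs; the incidence itself does differ. Likewise, a reader might infer that the late rate is understated in both arms, but that holds only against a hypothetical risk without death. What remains is that the SAP does not say which question it means to answer and offers no analysis for the hazard question.

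The size is also conditional. With equal survival there is no distortion between arms, and at low late-toxicity rates it is a point or less. The documents give no late-toxicity rate. Exponential survival is a simplification too: the BD survival cited in the protocol background, 47% at 2 years and 26% at 5, implies a hazard falling from −ln(0.47)/2 = 0.38 to ln(0.47/0.26)/3 = 0.20 per year.

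Three stronger readings are tempting, and the documents do not support them:
- That many patients will not have completed the window at the data cut. Protocol version 3 is dated June 2008, the active phase is planned at 4 years (section 8.6) and the primary analysis is planned for January 2015. If recruitment began around mid-2008 (assumed; no start date is shown), the last window would close around mid-2014.
- That late toxicity is the trial's main safety question. The protocol's rationale stresses grade 3 oesophagitis with twice-daily treatment (27% v 11%), and this point leaves the acute comparison untouched.
- That the SAP certainly plans a separate test of late toxicity. Its sentence places acute and late radiation morbidity together under acute toxicity, and can be read as one pooled proportion. Pooling would dilute the effect, but is itself a reason to clarify the wording.

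**Conclusion.** The point holds in a limited form. Late grade 3+ toxicity is compared only as a crude proportion over all patients given chemotherapy, with no stated rule for death and no analysis that allows for unequal time at risk. At the design survival and with equal late hazards, the expected OD:BD ratio is about 1.15 to 1.18: 0.5 to 1 point at 5-10% late risk and about 3 points at 30%. This rests on exponential survival, a constant and equal toxicity hazard, and the assumed completion times and risks. The effect shrinks with the survival gap and is nil when survival is equal. The planned proportion is valid as a description of burden; it is insufficient as the only comparison between arms. The change is worthwhile but does not touch the primary endpoint.

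**What to change.** In the SAP toxicity section:
- Analyse late toxicity separately from acute toxicity. Keep chi-squared and Fisher tests for acute toxicity.
- Keep the late proportion, or preferably cumulative incidence with death as a competing event, as the description of burden, and say that patients who die first count as not having had the event.
- For the comparison of late toxicity between arms, use time to first late grade 3+ event from the start of the window, among patients still at risk then, censored at death or last follow-up, by a cause-specific Cox model or log-rank test.

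Cumulative incidence alone would not do, because it carries the same survival effect as the crude proportion. The hazard comparison has its own limit: it conditions on patients surviving to the window, so it should be read beside the incidence.

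The cost is SAP wording and one extra analysis. The documents do not show that the follow-up form records onset dates (protocol section 6.5 says only when it is completed). Where it does not, event times are known only to the nearest visit, 3-monthly in the first year and 6-monthly after that (section 6.2). The analysis should state how such times are assigned.

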**[contact]**

**Randomisation by telephone:** The researcher calls the randomisation line and supplies a verbal password for the study. A checklist is checked over the telephone before randomisation. Randomisation will be performed using the computer system, callers will be advised of the patient's trial number and treatment allocation. Please record these on the eligibility checklist and return a copy to the trials office ([contact]). An e-mail confirmation will be sent to pre-arranged e-mail addresses for each centre.

**Randomisation by fax:** The randomization form must be completed, signed by an authorised member of staff and faxed to the fax randomisation line. On receipt of the fax staff at the trials office will check the eligibility checklist and perform the randomisation. An e-mail confirmation will be sent to pre-arranged e-mail addresses for that centre.

This trial is a comparison of treatment policies, once a patient has been randomised that patient remains in the trial and full documentation is always required. Inevitably some patients will stop treatment early, either because the patient does not wish to continue or because the responsible clinician feels it is not in the patient's best interest to continue. For patients who stop treatment early the responsible clinician should continue to complete as much clinical information as possible. As a minimum, follow-up data on progression and survival status should be returned regularly (unless explicit consent for this is withdrawn).

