### 4.1 CHEMOTHERAPY

Patients should start chemotherapy within two weeks of randomisation and within two weeks of a clinical assessment of fitness (section 4.1.1). Chemotherapy is cisplatin and etoposide and is given for 4 to 6 cycles. One cycle is given prior to radiotherapy. The second cycle in both arms is given concurrently with radiotherapy if possible. Radiotherapy will start on day 22 of cycle 1. In the BD radiotherapy arm, the third to sixth cycles (if applicable) are given after completion of the thoracic radiotherapy. In OD radiotherapy arm, the third & fourth cycles of PE are also given concurrently and the fifth & sixth cycles (if applicable) are given after completion of the thoracic radiotherapy.

Centres will be given the choice to stop chemotherapy after 4 cycles or to continue to up to 6 cycles. Centres who decide to give 6 cycles will have to continue doing so for all patients entered in the trial (unless it is decided that it is not in the patients best interest to receive cycle 5 and 6 or due to patient's choice)

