##### **Renal toxicity**

- Request GFR (*EDTA clearance*) before each course of chemotherapy ***If*** creatinine clearance < 50 ml/min
- If GFR re-estimated please dose according to the table:

| GFR              | Cisplatin                                               | Etoposide          |
|------------------|---------------------------------------------------------|--------------------|
| $\geq 50$ ml/min | Full dose                                               | Full dose          |
| 40-49 ml/min     | 50% dose reduction or substitute with carboplatin AUC 5 | 20% dose reduction |
| < 40 ml/min      | Off trial                                               | Off trial          |

**Other toxicities** (see appendix 2)

|                                                        |                                                                                                                       |
|--------------------------------------------------------|-----------------------------------------------------------------------------------------------------------------------|
| Peripheral neuropathy $\geq$ grade 2                   | Substitute carboplatin AUC 5 or 50% cisplatin dose reduction after recovery to $\leq$ grade 1; 100% dose of etoposide |
| Any grade 3-4 toxicities except mucocitis and alopecia | 25% dose reduction for cisplatin and etoposide after recovery to $\leq$ grade 1                                       |

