### 7.3.2 Qualifications for Analysis of Tumour Response

All patients meeting the following criteria will be evaluated for tumour response and included in the analysis of tumour response rates:

- treatment with at least one dose of cisplatin and etoposide.

**Response** will be assessed according to RECIST criteria (appendix 4) and the proportion of patients in each treatment group whose best response up to, approximately 28 days post cycle 4 or, if stopped prior to cycle 4, approximately 28 days after last chemotherapy cycle given, from randomisation is complete or partial will be compared using Chi-squared and Fisher Exact tests.

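### The SAP declares intention-to-treat but tests tumour response without randomised patients who never start chemotherapy; the effect is probably small and the fix is wording

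*Supplement*

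**What the plan says.** The SAP begins: "The analysis will be based on intention-to-treat principles (ITT". It states no exception there, and adds that patients are grouped by the arm assigned at randomisation. It then sets a population for each analysis:

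- **OS and local PFS:** "All randomised patients will be included in the analysis of overall survival (OS) and local progression free survival (ITT".
- **Tumour response:** "All patients treated with at least one dose of cisplatin and etoposide will be evaluated for tumour response and included in the analysis". Protocol 7.3.2, which sits under the efficacy heading of 7.3, has the same condition: "treatment with at least one dose of cisplatin and etoposide".
- **Safety:** "Safety analyses will be performed for all randomised patients treated with at least one dose of chemotherapy". This is slightly wider than the response set, because it does not name the drugs.

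The proportion with complete or partial response is compared between arms by chi-squared and Fisher exact tests. Best response is counted from randomisation. Neither document plans a response analysis in all randomised patients, or says how a patient outside the response set is to be counted.

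On timing, protocol 3.4 says of telephone randomisation that "callers will be advised of the patient's trial number and treatment allocation", and 4.1 says: "Patients should start chemotherapy within two weeks of randomisation".

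**The concern.** Membership of the response set is decided after randomisation, at a time when the site knows the arm. The text does not use the term open-label, but it follows: the allocation is disclosed, no blinding is described, and twice-daily treatment over 19 days is plainly distinguishable from once-daily treatment over 45 days (protocol 4.3.1 and 4.4.1).

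A patient who declines all treatment on learning the schedule, or who is lost for any other reason before the first dose, is outside the denominator. If that happens more often in one arm, the arm is judged on those who stayed. Protocol 3.4 describes the trial as comparing policies, with randomised patients remaining in it, and the response set does not follow that principle. What is at stake is one planned between-arm test, not the primary result.

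**Working it through.** **1. What the plan's own figures cover.** The documents give no figure for response. Only the sample size in protocol 7.1 can be reproduced, and here it serves only to fix the number per arm.

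- Freedman, HR 0.70, two-sided 5%, 80% power: (1.960 + 0.842)² × (1.70/0.30)² = 7.849 × 32.11 = 252.04, rounded up to 253 deaths. With 44% and 56% alive at 2 years the mean death probability is 0.50, and 253/0.50 = 506, as stated.
- The stated 247 deaths match Schoenfeld: 4 × 7.849/(ln 0.70)² = 31.40/0.1272 = 246.8.
- 506 × 1.05 = 531.3, rounded up to 532. With 1:1 allocation this is 266 per arm.

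None of these figures depends on the response set.

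**2. Who leaves the response set.** The condition is one dose of cisplatin and etoposide. Patients who stop after cycle 1 stay in, because the SAP gives a best-response window for those who stop before cycle 4. Only patients with no qualifying first dose are lost.

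**3. Size of the effect.** Let p be the response rate among starters, the same in both arms, and e the share of an arm that never starts. Both are assumptions.

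- Rate under the SAP's set: p in each arm, so the true difference among starters is 0.
- Rate in all randomised patients, with never-starters as non-responders: p × (1 − e).
- Shift in the arm difference: p × (difference in e).

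Worked example in whole patients, p = 80%, e = 1% v 3%: 3 v 8 patients never start, leaving 263 v 258. Responders are 210 v 206. The SAP's set gives 210/263 = 79.8% and 206/258 = 79.8%. All randomised gives 210/266 = 78.9% and 206/266 = 77.4%, a difference of 1.5 points.

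The table gives the arm difference in all randomised patients, in points, with the p-value of a pooled two-proportion z test (equivalent to chi-squared without continuity correction). Among starters every difference is zero apart from rounding to whole patients (at most 0.3 points). Which arm loses more is arbitrary.

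| Never start (patients) | p = 70% | p = 80% | p = 90% |
|---|---|---|---|
| 2% v 2% (5 v 5) | 0 | 0 | 0 |
| 1% v 3% (3 v 8) | 1.1 (0.78) | 1.5 (0.67) | 1.9 (0.50) |
| 2% v 5% (5 v 13) | 2.3 (0.58) | 2.6 (0.47) | 2.6 (0.37) |
| 0% v 5% (0 v 13) | 3.4 (0.40) | 4.1 (0.25) | 4.1 (0.15) |
| 0% v 10% (0 v 27) | 7.1 (0.08) | 8.3 (0.026) | 9.0 (0.003) |

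Balanced non-start produces no bias between arms and only overstates both rates: at 2% in each arm and p = 80%, 78.6% is reported as about 80%. With one arm losing up to 5% the shift is about 1 to 4 points, and no p-value falls below 0.05. Only the extreme case of 10% lost, all from one arm, could turn equal response among starters into a significant difference.

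**The case against.** The case for leaving the plan alone is substantial.

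- **Little reason to expect imbalance.** Cycle 1 is the same in both arms and radiotherapy starts on day 22 (protocol 4.1 and 4.2). A patient unhappy with the radiotherapy schedule can start chemotherapy, decline radiotherapy later and still be counted. Differential loss requires refusing all chemotherapy because of a schedule three weeks away. The documents give no sign of that. This stands, and it is why the effect is rated small. It does not show that the loss will be balanced.
- **The sets are prespecified.** A general ITT sentence followed by a named set for each analysis, with the ITT label attached only to OS and local PFS, can be read as a deliberate choice. Patients are also analysed by assigned arm for response, so only the all-randomised half of ITT is given up. On that reading the opening sentence is too broad, and the text still needs reconciling.
- **The loss will be visible.** The SAP and protocol 7.6 report patients treated by arm and the reasons for not being treated, so a reader could largely rebuild the all-randomised rate. That is true, but it does not change the denominator that is tested.
- **Response is not a listed endpoint.** This also stands. It remains a planned between-arm test.

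A reader might infer that anyone who drops out after learning the arm leaves the analysis. The text does not support that, because one dose is enough to stay in.

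A reader might also infer that patients given carboplatin are generally excluded, since the renal table allows "50% dose reduction or substitute with carboplatin AUC 5". That route is very narrow. Eligibility (3.3.2 k) requires normal creatinine and a clearance of at least 50 ml/min, so the patient would have to fall to 40–49 ml/min before cycle 1, be given carboplatin rather than reduced cisplatin, and never receive cisplatin afterwards. Later switches stay in. It is at most a wording mismatch between the response and safety sets.

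**Conclusion.** The point holds in a limited form. The SAP states ITT, yet its between-arm test of response omits randomised patients who never receive a first dose of cisplatin and etoposide, and the allocation is known before that dose.

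There is no bias between arms if non-start is balanced, and a shift of about 1 to 4 points for assumed imbalances of two to five percentage points. These sizes rest on an assumed 70–90% response among starters, 266 patients per arm, and never-starters counted as non-responders. The non-start rate cannot be estimated from the documents.

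It would be wrong to conclude that the trial's main result is at risk: OS and local PFS keep all randomised patients. This is a worthwhile tidy-up of low priority.

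**What to change.** In the SAP and in protocol 7.3.2, define the response population as all randomised patients by assigned arm, and state that never-treated patients and those without an assessable response count as non-responders. Treated patients without a scan already appear to be in the denominator under the present wording, so the main change is to add the never-starters and make the counting rule explicit.

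Report the rate among patients who started any protocol chemotherapy as a supporting figure. Using the same set as the safety analysis also removes the mismatch in drug wording.

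No new data are needed, because the disposition summary already requires the treated and untreated counts by arm. The cost is a slightly lower quoted response rate, by p × e in each arm (for example 0.80 × 2% = 1.6 points).
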